### **6.1. Planned Analysis**

Analysis of primary and secondary endpoints for the randomized BBN-102 w/o OPN Formula and Brand Formula groups will be performed at the end of the 16-week analysis. The 16-week analysis will use all efficacy and safety data collected for the BBN-102 w/o OPN Formula and Brand Formula groups. The analysis of BBN-001 w/ OPN Formula compared to the Brand Formula will occur separately depending on finalization of Generally Recognized as Safe (GRAS) approval of specific ingredients in BBN-001 w/ OPN Formula.

### **6.2. Reporting conventions**

P-values  $\geq 0.0001$  will be reported to 4 decimal places; P-values less than 0.0001 will be reported as “ $<0.0001$ ”. The mean will be reported to one decimal place greater than the original data. The standard deviation (SD) will be reported to two decimal places greater than the original data. Quantiles, such as median, Q1, Q3 or minimum (Min) and maximum (Max) will use the same number of decimal places as the original data. Estimated parameters, not on the same scale as raw observations (e.g., regression coefficients) will be reported to 3 significant figures.

### **6.3. Baseline Values**

Unless otherwise noted, baseline is defined as the last non-missing value recorded prior to the first feeding of the assigned formula.

### **6.4. Handling of Dropouts or Missing Data**

Subjects who are randomized in the study but never received an assigned formula will be considered dropouts. Dropouts will not be replaced.

All subjects who are randomized will be evaluated in the ITT population. Those subjects that do not complete the full study period due to protocol adherence or request to be discontinued from the study will not be replaced.

In general, analyses will be carried out with the data available with no imputation for missing data.

#### **6.4.1. Coronavirus Disease 19**

Due to the Coronavirus Disease 19 (COVID-19) outbreak during the course of the study, there may be several subjects who will have missing assessments which could affect the primary analysis. Subjects who are unable to attend a study visit due to COVID-19 will

be documented in the protocol deviation log. The protocol deviation date will be used as the COVID-19 affected date (or visit). If a subject reports an adverse event of COVID-19, then the event start date will be used as the affected date. In the event that a subject has an affected COVID-19 date from both sources, the earlier of the dates will be used.

Subjects who were affected by COVID-19 will be summarized in a data listing. The listing will contain the following information: subject number, formula, sex, age, first date affected by COVID-19, duration in study prior to the affected COVID-19 date, total study duration, exposure to study formula, any COVID-19 related adverse events, completion/discontinuation of the study, and reasons for discontinuation. All data listings will include a flag to denote whether the subject was affected by COVID-19.

### **6.5. Handling of repeat and unscheduled assessments**

Unscheduled assessments will be assigned to the associated visit and timepoint based on date and time of assessment. The assessment closest to the scheduled visit will be used for analysis.

### **6.6. Interim Analysis and Data Monitoring**

A blinded interim analysis of 81 subjects who completed 16 weeks of the study was performed in the first phase of the BBN-IF-001 study to estimate the standard deviation of weight gain. Based on this analysis, it is assumed that the standard deviation in weight gain is 6.0 g/day. No formal data monitoring is planned for this study.

### **6.7. Multiple Testing Procedure**

The secondary endpoints (growth velocities, growth z-scores, growth measurements, and formula intake) will be analyzed between Brand Formula and BBN-102 w/o OPN formula groups. Each secondary endpoint will be analyzed using the Hochberg step-up multiple testing procedure to control for the familywise error rate at level  $\alpha$ . The tests of statistical difference will be tested using a Hochberg corrected p-value.

### **6.8. Adjustments for Covariates**

Adjustments for sex, age at enrollment, baseline values, formula, visit, pooled site, formula by pooled site interaction, and formula by visit interaction will be made for statistical analyses. If the model does not converge when using all these covariates, then the formula by pooled site interaction term will be dropped from the model.

Some of the sites have very few subjects. All sites in the same state will be grouped together and then states will be grouped together geographically into a new pooled site variable.

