## **7.1 Inclusion Criteria**

Infants will be eligible to participate if they meet all of the following conditions. At birth the infant must be:

1. Healthy, term (no less than 37 weeks, 0 days and no greater than 42 weeks, 0 days), singleton infant
2. Have a birth weight of  $\geq$  2500 grams

At the time of the baseline/enrollment visit, infants must be:

3. Designated as healthy by a physician
4.  $\leq$  14 days post-natal age (Date of Birth = Day 0)
5. Weight for age  $\geq$  5th and  $\leq$  95th percentile for age according to World Health Organization (WHO) growth charts for infants and children ages 0 to 2 years of age
6. Length for age  $\geq$  5th and  $\leq$  95th percentile for age according to World Health Organization (WHO) growth charts for infants and children ages 0 to 2 years of age
7. Head circumference for age  $\geq$  5th and  $\leq$  95th percentile for age according to World Health Organization (WHO) growth charts for infants and children ages 0 to 2 years of age
8. Weight for length for age  $\geq$  5th and  $\leq$  95th percentile for age according to World Health Organization (WHO) growth charts for infants and children ages 0 to 2 years of age
9. Exclusively consuming and tolerating a cow's milk infant formula at time of enrollment; only infants whose parent(s) or legal guardian(s) have decided to feed infant formula as sole source of nutrition will be approached for potential study enrollment
10. Have parent(s) or legal guardian(s) who agree to feed the study formula as the sole source of nutrition for the duration of the study
11. Have parent(s) or legal guardian(s) who have read and voluntarily signed an Informed Consent form approved by the Institutional Review Board prior to any participation in the study.
12. Infants may be considered for enrollment again with a new baseline evaluation.

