## **8 PRIOR AND CONCOMITANT MEDICATION AND TREATMENT**

Infants who were previously breastfed can be enrolled provided they have discontinued breastfeeding at study entry, and parents agree that they have voluntarily chosen to exclusively formula-feed the study subject during the study. If formula-fed, infants must be currently receiving and tolerating cow's milk formula. At each study visit, site personnel will interview parent(s)/guardian(s) to obtain information about all concomitant therapy that was administered since the previous study visit. Concomitant medications include prescription medications, over-the-counter medications, and herbal supplements. Routine childhood immunizations will not be recorded as concomitant medications. This information will be recorded in the subject's medical record. If the infant was administered medication or treatment for a condition that may have an effect on the infants' growth and formula tolerance, the Investigator or medical staff must assess the potential medical implications to determine whether the study subject remains eligible to continue in the study. Use of an investigational product (i.e., therapeutic drug or vaccine) during a patient's participation in the study is prohibited. Participation in an observational or non-pharmaceutical/non-interventional trial (i.e. device trial) is allowed.

If a study subject was fed a formula other than the assigned study formula, this variation from protocol must be noted on the Protocol Deviation Log.

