### **9.2 Study Visit Procedures**

#### **Visit 1 (Day 0)**

- Informed consent process
- Inclusion/Exclusion criteria
- Demography
- Randomization
- Infant feeding history
- Physical exam
- Medical history
- Maternal smoking history
- Anthropometry (see Appendix A for data collection procedures)
- Stool Characteristics and Tolerance Questionnaire
- Infant Characteristics Questionnaire (ICQ)
- 3-day Formula/Diet Record
- Telephone contact
- Medications
- Adverse events
- Dispensing of study formula

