### **8.2. Demographic and Baseline Characteristics**

Demographics variables will include: age at enrollment, sex, ethnicity, race, and maternal smoking history. Age will be calculated by comparing date of birth to date of informed consent.

Baseline characteristics will include: anthropometry (weight, length, head circumference) and feeding history. Feeding history will include if child was ever breastfed, duration child was breastfed for, and infant's birth weight. All other feeding history information will be listed by subject. Initial visit assessments will also include a physical exam, a review of medical history, maternal smoking history, stool characteristics and tolerance.

Continuous variables will be summarized using descriptive statistics (mean, median, standard deviation, minimum, and maximum). Categorical variables will be summarized using counts and percentages.

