## 9.1. Primary Efficacy Analysis

The primary efficacy endpoint, mean daily weight gain (g/day) over the 16-week study period and at each study visit, will be calculated as (average weight in grams at each study visit – average weight in grams at baseline visit)/number of days since baseline visit. The weight is measured a minimum of two times at each study visit (a third weight is measured if the first two do not meet the threshold specified in the protocol). If two measurements are taken, then the average of the two will be used in the preceding formula. If there are more than two measurements, then the two measurements that are the closest will be averaged and used in the preceding formula. If three measurements are equidistant, then the lower two measurements will be averaged and used in the preceding formula. If there are less than 2 measurements recorded, then the average weight measurement will be set to missing. This average weight measurement will be used in the calculation for mean daily weight gain above. Descriptive statistics of the mean daily weight gain will be presented by visit and formula group. Mean daily weight gain at visit 9 (Day 120) will be compared between BBN-102 w/o OPN and the Brand Formula with a mixed-effect model for repeated measures (MMRM). The test for non-inferiority of the primary efficacy endpoint will have the following hypotheses:

H0: The difference (BBN-102 w/o OPN – Brand Formula) in mean daily weight gain between the formula groups is less than or equal to -3 g/day at visit 9 (Day 120).

H1: The difference (BBN-102 w/o OPN – Brand Formula) in mean daily weight gain between the formula groups is greater than -3 g/day at visit 9 (Day 120).

Formula groups will be compared using a MMRM with sex, age at enrollment, baseline value, formula, visit, pooled site, formula by pooled site interaction, and formula by visit interaction as factors. The covariance matrix will be chosen based on the Akaike Information Criterion (AIC) to choose the covariance matrix that best fits the model. Non-inferiority will be determined if the lower limit of the two-sided 95% CI for the difference (BBN-102 w/o OPN – Brand Formula) in least square means is greater than -3, assuming a non-inferiority margin of 3 g/day.

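### The primary model leaves out birth weight, which is already recorded, although about 93% of the Brand controls were not randomised against BBN-102

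*Supplement*

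**What the plan says.** **Model.** SAP V4 section 6.8 gives the general rule: "Adjustments for sex, age at enrollment, baseline values, formula, visit, pooled site", with formula-by-pooled-site and formula-by-visit interactions. Section 9.1 repeats it for the primary endpoint: "Formula groups will be compared using a MMRM with sex, age at enrollment, baseline value, formula, visit, pooled site". Neither list has birth weight, feeding history, maternal smoking or study phase.

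**What is collected.** SAP section 8.2: "Feeding history will include if child was ever breastfed, duration child was breastfed for", and the list ends with the infant's "birth weight. All other feeding history information will be listed by subject". The same section says "Demographics variables will include: age at enrollment, sex, ethnicity, race, and maternal smoking history". These items feed baseline summaries only. Protocol v5.2 section 7.1 makes a birth weight of at least 2500 g an entry condition. Section 8 says "Infants who were previously breastfed can be enrolled provided they have discontinued breastfeeding at study entry".

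**Endpoint.** Section 9.1 computes gain as visit weight minus baseline-visit weight, divided by days since baseline. Protocol section 7.1 caps age at entry at 14 days.

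**Control group.** SAP section 5 pools 129 phase-one Brand infants with about 10 from phase two, against about 86 on BBN-102, who are all in phase two.

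**Checks planned.** Section 9.1.1 has two sensitivity analyses: excluding COVID-affected infants, and multiple imputation. Section 9.1.2 compares unadjusted Brand gain between phases. None of these adds a covariate.

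**The concern.** Gain is counted from entry weight in the first two weeks of life. Two infants of the same sex, age and entry weight can have different birth weights, so one may be below its birth weight and the other above. If infants below birth weight make up the shortfall, the first shows a larger gain per day for reasons unrelated to formula. Early weight loss and regain is general physiology; the documents do not mention it.

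In a fully randomised comparison such a difference would be left to chance, and omitting the covariate would cost only precision. Here most of the comparison is between enrolment periods. Recruitment may have differed between them in ways that entry age and entry weight do not fully capture. At stake is a residual shift in the difference that is tested against the 3 g/day margin.

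**Working it through.** **Inputs (SAP section 5).** 64 BBN-102 and 104 Brand evaluable, SD 6.0 g/day, margin 3 g/day, one-sided alpha 0.025, 25% attrition, power approximately 90%.

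**1. The plan's own figure.**
- SE = 6 × sqrt(1/104 + 1/64) = 0.953 g/day.
- Power = Φ(3/0.953 − 1.96) = 88.2% (87.9% by noncentral t). This fits the stated approximate 90%.
- 64/0.75 gives 86 and 104/0.75 gives 139, as stated.

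**2. How much of the comparison is randomised.**
- Phase-one share of Brand: 129/139 = 92.8% enrolled, 96/104 = 92.3% evaluable.
- Concurrent comparison alone, about 8 vs 64: power 26.5%. Its information relative to the pooled comparison is (1/104 + 1/64)/(1/8 + 1/64) = 18%.

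**3. What birth weight would add.** With entry weight in the model, adding birth weight is the same as adding the deficit (birth weight minus entry weight). The bias from leaving it out is:

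bias = f × Δ / 120

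Here Δ is the difference between groups in mean deficit that remains *after* adjustment for age, entry weight, sex and pooled site, and f is the share of the deficit that appears as extra gain by Day 120. The documents give neither f nor Δ.

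**4. Upper-end illustration.** Assume f = 0.5-1 and an *unadjusted* shift of 50-100 g:
- Bias: 0.5 × 50/120 = 0.21 to 1 × 100/120 = 0.83 g/day, or 7-28% of the margin.
- False non-inferiority at a true difference of −3, with the bias favouring BBN-102: Φ(0.21/0.953 − 1.96) = 4.1% to Φ(0.83/0.953 − 1.96) = 13.9%.

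These figures put the raw shift in place of Δ, so they take no account of what age and entry weight already remove.

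**5. Scale for any residual bias that survives adjustment** (values assumed; grams at Day 120 = bias × 120):

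| Residual bias, g/day | Grams at Day 120 | False non-inferiority if it favours BBN-102 | Power if it goes against BBN-102 |
|---|---|---|---|
| 0 | 0 | 2.5% | 88.2% |
| 0.1 | 12 | 3.2% | 86.0% |
| 0.25 | 30 | 4.5% | 82.3% |
| 0.5 | 60 | 7.6% | 74.6% |
| 1.0 | 120 | 18.1% | 55.5% |

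**6. Precision.** Assume a deficit SD of 100-200 g and f = 0.5-1. The SD contribution is f × SD/120 = 0.42-1.67 g/day, and R² = contribution²/36 = 0.5-7.7%. Power = Φ(3/(0.953 × sqrt(1 − R²)) − 1.96) = 88.4-90.6%. This also ignores the existing covariates.

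**7. Can section 9.1.2 settle it?** With about 8 phase-two and 96 phase-one Brand infants, the SE of the phase difference is 6 × sqrt(1/8 + 1/96) = 2.21 g/day, a 95% half-width of 1.96 × 2.21 = 4.3 g/day. That is wider than the margin, and the check does not look at baseline factors.

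**The case against.** The strongest reply is that the model already holds age at enrollment, baseline value, sex and pooled site. Differences in discharge or recruitment timing act largely through age at entry. A reader might infer that a phase difference in deficit passes undiminished into the Day 120 result, or that 0.2-0.8 g/day and 4-14% are the effect of the omission. The documents support neither: only the part left after adjustment counts, and every driving input is assumed. The top figure needs a 100 g mean shift, full carry-over and the favourable direction. That shift is 0.5-1.0 SD on the assumed deficit SD of 100-200 g, and nothing in the documents indicates one. This part of the reply stands.

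It also stands that breastfeeding history and smoking have no quantified effect. Maternal smoking is missing from the Visit 1 list of the earliest protocol in the supplement, although the 2019 SAP summarises it, so its completeness in early phase-one controls is uncertain. The precision gain is minor.

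Section 8.2 would show an imbalance in birth weight between formula groups. It plans no table of entry weight minus birth weight and no split by phase, and a table does not adjust the estimate. The existing covariate set is defensible, but that does not explain leaving out a relevant baseline the trial already holds when 93% of controls are non-concurrent.

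**Conclusion.** The point holds for birth weight, as a modest and inexpensive improvement. The primary model omits a recorded, eligibility-checked baseline that separates infants of equal entry weight and age. Randomisation does not protect the comparison for 129 of 139 Brand infants. A residual imbalance between phases is possible; its size and direction cannot be derived from the documents. The 0.2-0.8 g/day and 4-14% figures are upper-end, rest only on assumptions and ignore the existing adjustment. Power would move from 88.2% to at most about 90.6%.

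Two further assumptions apply. The baseline value in 9.1 is read as entry weight, which is natural because a velocity has no value at baseline, but the SAP does not say so. Birth weight is taken as nearly complete because eligibility depends on it.

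A reader might also infer that these covariates would make the phase-one controls comparable. They would not. They address imbalance in measured factors only, and calendar-time differences between phases remain.

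**What to change.** Before unblinding:

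1. In 6.8 and 9.1, add birth weight as a covariate next to entry weight in the primary MMRM. At minimum, pre-specify this as a sensitivity MMRM for the primary endpoint in 9.1.1. State how a missing birth weight is handled, for example by giving it the overall mean, so that no infant is lost.
2. State that the baseline value in 9.1 is entry weight.
3. In 8.2, tabulate birth weight and entry weight minus birth weight by formula and by phase.
4. Keep ever breastfed and maternal smoking for one supportive sensitivity model, each with a missing category so that phase-one Brand infants are not dropped.

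The cost is SAP wording, one table and one or two extra model runs. Birth weight uses one degree of freedom, and no new data are needed. If the blind is already broken, SAP section 6 requires the added analysis to be labelled post hoc. The non-concurrent control issue needs its own treatment.

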## 7. Analysis Populations

- Intent to Treat (ITT): All randomized subjects in the study based on the formula group they are randomized to.
- Per Protocol (PP): A subset of the ITT population. It will consist of all subjects who complete the feeding protocol without significant protocol violations, have weight measurements at both baseline and Week 16, and who consume a single non-study formula feeding no more than 10 times during the duration of 16-week study as documented on the Other Than Formula Feeding Log. Additionally, subjects who consume more than 3 complete days of non-study formula, defined as greater than 50% (4 feedings) of the number of feedings in a 24-hour period from non-study formula, will also be excluded from the PP population. Inclusion criteria states that four anthropometric Z-scores (weight for age, length for age, head circumference for age, and weight for length) had to be  $\geq 5^{\text{th}}$  and  $\leq 95^{\text{th}}$  percentile. If two or more of the four anthropometric Z-score inclusion criteria are not met, it will be considered a significant protocol violation and the infant will be excluded from the Per Protocol population.

Given that some sites rely on paper growth charts (hand plotting) of anthropometric measures, occasional small errors may occur with subjects just slightly outside the 5th or 95th percentile being enrolled in the study. If only one of the four anthropometric Z-score inclusion criteria are not met, it will be considered a minor protocol violation and the infant will remain in the Per Protocol population.

- Safety Population: The safety population will be comprised of any subjects who are randomized and consumed at least one feeding of study formula.

Classification into ITT or PP populations will be conducted prior to the database lock. All listings will be provided for the ITT population. A separate listing will be included on the set of subjects who are randomized but never intake the randomized formula before discontinuing from the study.

Since this study has a primary aim at demonstrating non-inferiority, the PP population will represent the primary analysis population to evaluate the treatment groups in terms of “efficacy”.

All clinical outcomes (primary and secondary) will be subject to analyses using both the PP and ITT population.

## **8. Subject Characteristics**

### **8.1. Subject Disposition**

Information regarding subject disposition will be summarized for all subjects by treatment group. Summaries will include: number of subjects enrolled, number of subjects in each analysis population, number of subjects completing the study, number of subjects who discontinue the study early. For those who discontinue early, the primary reason for discontinuation will be summarized.

### **8.2. Demographic and Baseline Characteristics**

Demographics variables will include: age at enrollment, sex, ethnicity, race, and maternal smoking history. Age will be calculated by comparing date of birth to date of informed consent.

Baseline characteristics will include: anthropometry (weight, length, head circumference) and feeding history. Feeding history will include if child was ever breastfed, duration child was breastfed for, and infant's birth weight. All other feeding history information will be listed by subject. Initial visit assessments will also include a physical exam, a review of medical history, maternal smoking history, stool characteristics and tolerance.

Continuous variables will be summarized using descriptive statistics (mean, median, standard deviation, minimum, and maximum). Categorical variables will be summarized using counts and percentages.

